### 2.6. Data Collection

The data required for evaluating the influences of Deqi on acupuncture therapy will be collected at baseline and the completion of intervention. Data will be obtained via physical measurements. Data collection instruments and the study timeline are summarized in Table 1.

A case report form (CRF) has been designed, to include the variables of interest, which will be completed by the corresponding researcher at each research center. After the trial finished, the information obtained will be input to an electronic database, for subsequent statistical analysis.

### 2.7. Data Storage and Confidentiality

All CRFs will be stored in a locked cabinet at a study office in School of Acupuncture, Moxibustion and Tuina, Beijing University of Chinese Medicine, and will have a unique identification number. Data will be input to an electronic database, and the access to the database is restricted to the study team.

### 2.8. Statistical Analysis

All analyses will be performed using SPSS 17.0 (SPSS Inc., Chicago, IL). Potential differences across study groups on demographic and clinical history variables will be compared by means of analysis of covariance (ANCOVA). Repeated-measures analysis of variance (ANOVA) will be utilized for the analysis of VAS-P and VAS-A scores and temperatures at SP6 (Sanyinjiao) as well as CV4 (Guanyuan) acupoint. *P* < 0.05 will be denoted as significant.

Although most participants of the Deqi group will experience Deqi, there will probably be some exceptions that participants in the group will not experience Deqi. Therefore, we will redivide all participants into the real Deqi group and unreal Deqi group according to a self-designed Acupuncture Deqi Clinical Assessment Scale (ADCAS) grade after treatment. We will perform a secondary analysis with similar statistical method to explore whether the real Deqi has influences on the effect of acupuncture. We will compare the first and second analysis results.

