Acupuncture is one of the main treatment modalities of TCM. Several trials [21, 22] have already demonstrated the encouraging results of acupuncture as a nonpharmacological option for the treatment of PD. Two systematic reviews also demonstrated the effect [23] and cost-effectiveness [24] of this therapy. The acupoint SP6 (Sanyinjiao) is found to be one of the most commonly used points encountered when searching ancient Chinese medical classics, Chinese acupuncture textbooks, and clinical trials using acupuncture-related therapies for PD [25, 26]. Previous randomized controlled trials have showed that acupuncture at SP6 (Sanyinjiao) can relieve the pain of PD immediately [27–29] especially for PD patients with Cold and Dampness Stagnation pattern [30], which is the most common pattern in PD patients [31, 32]. Langevin's study [7] also showed that, compared with the nonacupoint control group, the average pullout force in SP6 (Sanyinjiao) was greater, which suggested that SP6 (Sanyinjiao) might be especially sensitive in Deqi.

In this study, we will perform a randomized controlled trial using SP6 to investigate the influences of Deqi on immediate analgesia effects in PD patients with Cold and Dampness Stagnation pattern. The primary objective of this trial is to evaluate the influences of Deqi on acupuncture therapy, in terms of pain reduction (measured on a 0–100 mm visual analogue scale for pain (VAS-P)) achieved before and after intervention (i.e., before and after 30 minutes of treatment). The secondary objectives are as follows: (1) to evaluate the influences of anxiety reduction on a 0–100 mm visual analogue scale for anxiety (VAS-A) and (2) to evaluate the influences of temperature changes at SP6 (Sanyinjiao) and CV4 (Guanyuan) acupoints monitor by a digital infrared thermographic imaging device (only in the Dongzhimen Hospital).

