### 2.3. Randomization and Blinding

The central randomization will be performed by the Center for Evidence-Based Chinese Medicine affiliated to Beijing University of Chinese Medicine in China, using complete randomization to generate the random allocation sequence. Once a participant is included, the researcher will contact the randomization center for the group allocation of the participant, and the acupuncturist will be informed by telephone. Participants will be allocated at a 1 : 1 ratio (Figure 1).

The participants will be informed that they will have a 50% chance of being allocated in either of the two acupuncture groups, and both groups will be potentially effective; hence, participants will be blinded to the group allocation. The patients will also be informed of the possible risks associated with acupuncture (hematoma or fainting). The acupuncturist cannot be blinded due to the specific nature of intervention. Outcome assessors and personnel who will deal with data collection and data analysis will be blinded throughout the entire trial.

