### 2.4. Interventions

All participants, when their VAS-P score of menstrual pain is equal to or more than 40 mm on the first day of menstruation, will each receive an acupuncture treatment for 30 minutes at bilateral SP6 acupoints. The SP6 lies on the tibial aspect of the leg, is posterior to the medial border of the tibia, and is 3 B-cun (proportional bone cun) superior to the prominence of the medial malleolus [35].

*(a) Deqi Group*. The treatment will be performed after sterilizing the skin on the areas where the needles will be inserted, with participants lying face up. Using single-use sterile needles (Zhongyan Taihe, Wuxi Jiajian Medical Instrument Co. Ltd., Jiangsu, China) of 0.30 mm calibre and 40 mm length, a needle will be vertically inserted 1 cun in depth and will be manipulated by lifting-thrusting and twirling methods for 30 seconds to achieve Deqi.

*(b) No Deqi Group*. Single-use sterile needles (Zhongyan Taihe, Wuxi Jiajian Medical Instrument Co. Ltd., Jiangsu, China) of 0.18 mm calibre and 13 mm length will be used. The treatment will be performed after sterilizing the skin on the areas where the needles will be inserted, with participants lying face up. A needle will be vertically inserted 0.1 cun in depth. No manipulation will be performed after insertion of needles to avoid Deqi.

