### 2.5. Outcome Measures

#### 2.5.1. Primary Outcome Measures

The changes of pain will be measured by visual analogue scale for pain (VAS-P), before and after the treatment. The validity and reliability of the VAS-P scale have been proven [36–38] and it was employed in our previous similar studies [29, 30]. The scale measures a continuous quantitative variable varying from 0 mm (no pain) to 100 mm (worst pain ever).

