## Figures and Tables

**Figure 1 fig1:**
[figure not shown]
Flow diagram for the study. Work scheme with description of assessment visits and times.

**Table 1 tab1:** Data collection at different assessment points. Example of outcome measurements.

Variable	T0	T1
VAS-P	X	X
VAS-A	X	X
ADCAS		X
Temperature at SP6, CV4	X	X
Side effects and adverse reactions		X
Sociodemographic data	X	

Note: VAS-P: visual analogue scale for pain (0–100); VAS-A: visual analogue scale for anxiety (0–100); ADCAS: Acupuncture Deqi Clinical Assessment Scale; SP6: Sanyinjiao; CV4: Guanyuan; T0: before acupuncture treatment; T1: after acupuncture treatment.

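### Pain is measured only before and after one session, yet VAS-P goes to repeated-measures ANOVA: a valid test of change, but generally less efficient than ANCOVA on the baseline score already collected

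*Protocol article*

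**What the plan says.** Section 2.8 gives one method for all the continuous outcomes: "Repeated-measures analysis of variance (ANOVA) will be utilized for the analysis of VAS-P and VAS-A scores", and the same for the temperatures at SP6 and CV4. ANCOVA appears once, for baseline characteristics: "Potential differences across study groups on demographic and clinical history variables will be compared by means of analysis of covariance (ANCOVA". The significance rule is that P < "0.05 will be denoted as significant".

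There are two assessments, as the note to Table 1 shows: "T0: before acupuncture treatment; T1: after acupuncture treatment". Section 2.5.1 defines the primary outcome: "The changes of pain will be measured by visual analogue scale for pain (VAS-P), before and after the treatment". The primary objective in the Introduction is likewise pain reduction "achieved before and after intervention (i.e., before and after 30 minutes of treatment".

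Two design features bear on the analysis. Section 2.3 states "Participants will be allocated at a 1 : 1 ratio". Section 2.4 gives the treatment "when their VAS-P score of menstrual pain is equal to or more than 40 mm on the first day of menstruation", so T0 scores are cut off from below.

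**The concern.** With one measurement before treatment and one after, repeated-measures ANOVA treats the T0 score as a second outcome, although treatment cannot have affected it. ANCOVA uses T0 as a predictor and removes from the T1 comparison only as much variation as T0 explains. A raw change score fixes the slope on T0 at 1. When the true slope is below 1, it adds noise to the comparison.

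The model also yields a group main effect, which averages T0 with T1 and estimates only half the treatment effect. That term would be a poor basis for the primary conclusion.

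ANCOVA meanwhile goes to demographic and history variables, where it serves no purpose: under randomisation any group difference on them is due to chance.

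What is at stake is precision on the primary outcome in a trial that targets 40 patients per group.

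**Working it through.** **Inputs from the document.** There are two time points (Table 1), 1:1 allocation (section 2.3), a significance level of 0.05 (section 2.8) and a target of 40 per group (section 2.2.1). The only stated size figure can be reproduced: 40 × 1.20 = 48 per group, 96 in total. It rests on no effect size, SD or power, so there is no stated power to reproduce.

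**Assumptions, not in the document.** Two-sided testing, 40 completers per group, and a T0–T1 correlation r of 0.3, 0.5 or 0.7. In steps 1 to 4 the SD is the same at T0 and T1.

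**Step 1: variances per patient.** With unit SD and treatment effect δ at T1:
- ANCOVA of T1 on T0 estimates δ with variance 1 − r².
- Group × time (the t-test on change) estimates δ with variance 2(1 − r).
- The group main effect (mean of T0 and T1) estimates δ/2 with variance (1 + r)/2.

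**Step 2: change score against ANCOVA.** The variance ratio is 2(1 − r)/(1 − r²) = 2/(1 + r).
- r = 0.3: 2/1.3 = 1.54
- r = 0.5: 2/1.5 = 1.33
- r = 0.7: 2/1.7 = 1.18

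The relative efficiency is the inverse, (1 + r)/2: 0.65, 0.75 and 0.85.

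**Step 3: power.** Set δ so that ANCOVA has 80% power with 40 per group (noncentral t):

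| r | ANCOVA | Group × time | Group main effect |
|---|---|---|---|
| 0.3 | 80% | 62% | 38% |
| 0.5 | 80% | 68% | 29% |
| 0.7 | 80% | 73% | 19% |

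The last column shows only what would follow if that term were used. Its efficiency relative to ANCOVA is (1 − r)/2: 0.35, 0.25 and 0.15.

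**Step 4: illustration in millimetres.** Assume a 12 mm effect and an SD of 20 mm. Power for ANCOVA against group × time is 80% vs 62% at r = 0.3, 87% vs 77% at r = 0.5, and 96% vs 93% at r = 0.7. A simulation of 4,000 trials per correlation gave 78% vs 61%, 86% vs 75% and 96% vs 93%. At r = 0.5, 80% power needs 33 per group with ANCOVA and 44 with group × time.

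**Step 5: effect of the 40 mm rule.** In general, var(change) = residual variance + (1 − β)² × var(T0), where β is the slope of T1 on T0. The ANCOVA variance is the residual variance alone. Under a linear model with constant residual variance, selecting on T0 leaves β and the residual variance unchanged and shrinks var(T0), so the penalty falls.
- Before selection, unit SDs and r = 0.5: β = 0.5 and residual 0.75. The ratio is (0.75 + 0.25 × 1)/0.75 = 1.33.
- With var(T0) halved: (0.75 + 0.25 × 0.5)/0.75 = 0.875/0.75 = 1.17.
- The correlation drops to 0.25/√(0.5 × 0.875) = 0.38. Putting 0.38 into the equal-SD formula would give 2/1.38 = 1.45, which is the wrong direction.

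A second case assumes SD 14 mm at T0, SD 22 mm at T1 and a 12 mm effect:
- r = 0.3: β = 0.3 × 22/14 = 0.47, residual 484 × 0.91 = 440, penalty 0.53² × 196 = 55. The ratio is 495/440 = 1.12, and power is about 73% vs 67%.
- r = 0.5: β = 0.5 × 22/14 = 0.79, residual 484 × 0.75 = 363, penalty 0.21² × 196 = 9. The ratio is 372/363 = 1.02, and power is about 80% vs 80%.

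**The case against.** The strongest defence is that the planned test is sound. Sections 1 and 2.5.1 define the outcome as change in pain, and a group comparison of change is the group × time term. That test is unbiased under randomisation. This stands, and it limits the point to efficiency.

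A reader might infer that the primary result will be diluted by half, or that a fall in pain over time will be reported as an analgesic effect. The document supports neither. It nowhere says that the group main effect or the time effect will decide the question, and its outcome definition points elsewhere. Section 2.8 does not name the deciding term, but a condensed article may leave that to the full protocol or analysis plan, so the silence is not a fault in itself. What remains is a caution that the main effect should not be the deciding term.

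A reader might also infer that the 40 mm rule worsens the loss by lowering the T0–T1 correlation. Step 5 of the working shows the reverse: the correlation falls, but so does the penalty.

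Finally, no stated power is undermined, because section 2.2.1 states none; the 80% benchmark is a device for comparison. This also stands. It does not rescue the choice, which is a stated method rather than an omission, since a better use of the same data costs nothing. The use of ANCOVA on baseline variables does not affect the primary result.

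**Conclusion.** The point holds as an efficiency weakness of should-fix weight. Section 2.8 chooses a model whose relevant term is a t-test on unadjusted change, although the T0 score is available as a covariate.

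With equal SDs, the choice costs the equivalent of 35%, 25% or 15% of the patients at r = 0.3, 0.5 or 0.7 (one minus the relative efficiency). These figures are illustrative: effect size, SDs and correlation are all assumed. The narrowed T0 range probably makes the loss smaller, and it approaches zero when the slope of T1 on T0 is near 1. The direction is firm and the size is not. The documents do not support calling the primary test invalid or biased.

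**What to change.** In section 2.8, or in the analysis plan before the data are analysed:
- Make the primary analysis an ANCOVA of T1 VAS-P on randomised group with T0 VAS-P as covariate, and report the adjusted mean difference with its 95% CI.
- Use the same model for VAS-A and for the temperature at each acupoint, each with its own T0 value as covariate.
- Describe demographic and history variables by group, without significance tests.
- If repeated-measures ANOVA is kept, name group × time as the term that tests the hypothesis.

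The cost is a change of wording. Both T0 and T1 values are already scheduled in Table 1, so no further data or patients are needed, and the model runs in the software that section 2.8 names.

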## 3. Discussion

The trial is designed to illustrate Deqi effect on acupuncture treatment. It will estimate Deqi state of solo acupoint and compare analgesic right after needling. All participants will be randomly divided into Deqi or no Deqi group. Unlike other impact factors of acupuncture treatment, Deqi is a group of specific subjective sensations which can only be felt during acupuncture by both patients and acupuncturists. It is impossible to randomly allocate participants into a Deqi or no Deqi group, so there have been no Deqi randomized controlled trials (RCTs). However, whether Deqi can be achieved during acupuncture can be predicted to a certain extent; therefore, we will randomly divide all participants into Deqi or no Deqi group. We also employ manipulation technique to promote Deqi in the Deqi group, while in the no Deqi group we avoid Deqi according to TCM theory and experts' experience.

In this study, we will use an important self-designed instrument—Acupuncture Deqi Clinical Assessment Scale (ADCAS). The scale shows the intensity of participants' sensation, ranging from 0 to 4: 0 (no), 1 (slight), 2 (mild), 3 (obvious), and 4 (strong). It will be firstly used as an instrument for redividing all the included participants in reanalysis. Actually, some researchers and their colleagues have attempted to qualify and quantify sensations of Deqi [41–47] and designed several Deqi scales or questionnaires like the Vincent scale, the Park questionnaire, the MGH Acupuncture Sensation Scale (MASS), and Southampton Needling Sensation Questionnaire (SNSQ). Some of the scales or questionnaires have been used in Deqi trials [48–50] and MASS even has a Chinese edition [51]. However, though Deqi sensation can be felt by patients and acupuncturists, all the current scales take no consideration of the Deqi sensation felt by acupuncturists' hands, which decreases the reliability of those scales.

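### The exploratory real-versus-unreal Deqi comparison regroups both arms on a post-treatment grade with no stated term for randomised arm, so it can show a Deqi effect when there is none

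*Protocol article*

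**What the plan says.** Section 2.8 plans two analyses. The main one compares the randomised groups on VAS-P, VAS-A and acupoint temperatures by repeated-measures ANOVA. The other allows for patients in the Deqi arm who do not feel Deqi: "we will redivide all participants into the real Deqi group and unreal Deqi group according to a self-designed Acupuncture Deqi Clinical Assessment Scale (ADCAS"). Its purpose and method are given as "We will perform a secondary analysis with similar statistical method to explore whether the real Deqi has influences on the effect of acupuncture". Section 2.8 then adds: "We will compare the first and second analysis results".

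Table 1 lists ADCAS at T1 only, the time point of the post-treatment VAS-P. Its note reads "T0: before acupuncture treatment; T1: after acupuncture treatment".

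Under section 2.4 the arms differ in more than the intended sensation. The Deqi arm uses needles "of 0.30 mm calibre and 40 mm length, a needle will be vertically inserted 1 cun in depth", which "will be manipulated by lifting-thrusting and twirling methods for 30 seconds to achieve Deqi". The No Deqi arm uses a needle of 0.18 mm by 13 mm, inserted 0.1 cun and not manipulated.

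The Discussion accepts that Deqi itself cannot be randomly allocated. The article states no adjustment for or stratification by randomised arm in the regrouped analysis, and no caution that it is a non-randomised comparison.

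**The concern.** The grouping variable is a response to treatment, recorded alongside the outcome. Two biases follow.

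1. **Technique.** Section 2.8 expects most of the Deqi arm to feel Deqi, and the control technique was chosen to avoid it. The real Deqi group will therefore hold mainly patients needled deeply with manipulation, and the unreal group mainly patients needled shallowly without it. With no arm term, any effect of needle, depth or manipulation that does not act through Deqi is partly credited to Deqi.
2. **Patient.** People who feel Deqi readily may also respond better, or worse, for other reasons. Randomisation balances this between arms, but not between groups formed by the sensation itself.

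The stake is interpretation. The trial aims to explain the role of Deqi in analgesia, and this is the planned analysis that looks directly at felt Deqi. If its contrast is larger than the randomised one, readers may take the gap as evidence for Deqi, although bias alone could produce it.

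**Working it through.** **Inputs from the article.** Allocation is 1:1 (section 2.3) and alpha is 0.05 (section 2.8). Section 2.2.1 gives 40 per group and 20% dropout, and its total reproduces: 40 × 1.20 = 48 per group, 96 in all. That figure serves below only as the group size for simulation; the shares in step 1 do not depend on it.

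**Assumptions, not in the article.** Deqi rates p1 (Deqi arm) and p0 (No Deqi arm); a technique effect T of 10 mm; SD 20 mm; and, in step 2, a prognostic effect of 5 mm per SD of proneness to Deqi. The true effect of Deqi is set to 0 throughout.

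**Step 1. Technique.** With 1:1 allocation, the Deqi arm supplies p1/(p1+p0) of the real group and (1−p1)/(2−p1−p0) of the unreal group. The spurious difference is

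T × [p1/(p1+p0) − (1−p1)/(2−p1−p0)].

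- 90%/10%: 0.90 − 0.10 = 0.80, or 8.0 mm
- 80%/20%: 0.80 − 0.20 = 0.60, or 6.0 mm
- 70%/30%: 0.70 − 0.30 = 0.40, or 4.0 mm
- 80%/40%: 0.667 − 0.250 = 0.417, or 4.2 mm

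In 5,000 simulated trials per setting (40 per arm, two-sided t-test on VAS-P reduction), the regrouped contrast was significant in 41%, 26%, 14% and 14% of runs, in that order. With only T0 and T1, a t-test on change is the group-by-time test of a repeated-measures ANOVA, so it matches the stated method.

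**Step 2. Patient.** Now T = 0, and proneness is a standard normal variable that sets who feels Deqi. The simulated spurious differences were 3.5, 5.5, 6.9 and 6.9 mm in the same order, with false-positive rates of 12%, 23%, 34% and 32%. The randomised comparison stayed at about 0 mm and 5%.

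With neither a technique nor a proneness effect, the regrouped contrast was also about 0 mm and 5%.

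**Step 3. What an arm term does.** With randomised arm in the model, the step 1 bias goes: a fresh simulation gave between −0.2 and 0.0 mm, with about 5% significant at every pair of rates. The step 2 bias does not go. At 80%/20% the standard normal density at the threshold is 0.280. Within an arm, patients with and without Deqi differ in mean proneness by 0.280/(0.8 × 0.2) = 1.75 SD, or 5 × 1.75 = 8.75 mm. Without the arm term the figure is 5 × (0.560 + 0.560) = 5.6 mm. Adjustment therefore removes confounding by technique and can enlarge confounding by patient.

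**Step 4. Precision.** At 80%/20% the correlation between arm and Deqi status is 0.60. Adding arm multiplies the standard error by 1/√(1 − 0.36) = 1.25. At 90%/10% the correlation is 0.80 and the factor is 1/√(1 − 0.64) = 1.67.

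**The case against.** The strongest reply is that this analysis is labelled secondary and exploratory, that the comparison by randomised group comes first, and that the Discussion concedes Deqi cannot be randomised. All of that stands. A reader might infer that the trial's main result is biased or its randomisation broken. It is not: the regrouping leaves the randomised comparison untouched.

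A second reply is that confounding with technique is not peculiar to the regrouping. This also stands. In step 1, where Deqi does nothing, the randomised contrast shows the full 10 mm and the regrouped one 6.0 mm at 80%/20%. The randomised contrast is a valid estimate of the package of needle, depth, manipulation and Deqi, but it does not isolate Deqi.

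Third, the sizes are assumed. The article gives no Deqi rate, technique effect or SD, so neither the size nor the direction of the bias can be derived from it.

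Two further readings are tempting and not supported:

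- No threshold on the 0–4 grade is given, so one might suspect that the split could be chosen after seeing results. An article commonly leaves such a threshold to the full protocol or SAP, and nothing says that several splits will be tried.
- The Discussion faults existing instruments because "all the current scales take no consideration of the Deqi sensation felt by" acupuncturists' hands. One might conclude that the unblinded acupuncturist helps to decide the group. The ADCAS items are not shown, and the article describes the scale as grading the participant's sensation.

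What the objections do not remove is that a non-randomised contrast is to be analysed like the randomised one, with no arm term stated, and set beside it without a caution.

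**Conclusion.** The point holds for the real-versus-unreal Deqi comparison only. As worded, that comparison passes 0.40 to 0.80 of any technique effect into the apparent Deqi effect at the Deqi rates tried, and adds any prognostic difference between patients who do and do not feel Deqi. It can therefore show a Deqi effect when there is none. The shares follow by algebra from the assumed rates; the millimetre and false-positive figures also rest on the assumed 10 mm, 5 mm per SD and SD of 20 mm. If neither technique nor proneness to Deqi affects pain, there is no bias. This is a cheap improvement to a secondary analysis, not a fault in the primary one.

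**What to change.** Reword the second part of section 2.8:

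- Analyse T1 VAS-P by ADCAS grade or group with randomised arm and T0 VAS-P in the model, and show the ADCAS association within each arm.
- Report it as an observational association in which patient-level confounding remains. Step 3 shows why an arm term alone does not justify a causal claim.
- State that a difference between the two analyses will not be read as proof of a Deqi effect.
- Rest the trial's conclusion on the randomised comparison, described as a comparison of technique packages.

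No new data are needed, since arm, T0 and T1 VAS-P and ADCAS are already collected. The cost is precision (a standard error about 1.25 times as large at 80%/20% and 1.67 times at 90%/10%) and a weaker claim about Deqi.
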